### • **Intention-to-treat analysis:**

All inclusions (valid cases + dropouts). All parameters collected are analysed.

### • **Per-protocol analysis:**

All inclusions without meeting a drop-out criterion (all valid cases). All parameters collected are analysed. The per-protocol analysis is the primary evaluation concept.

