## 6.1 Data analysis and evaluation

The data obtained will be analysed using IBM SPSS, version 27. A descriptive data description (mean, standard deviation, percentile rank) will be provided. Correlations between variables will be calculated using Pearson's correlation coefficient or Spearman's correlation coefficient, depending on the distribution. Error probabilities below  $p < 0.5$  are considered statistically significant. Microbiome analyses are performed in R (version 3.6) and Rstudio (version 1.2.1555) (R-doundation, Vienna, Austria), with visualisations using the ggplot2 library.

Both an intention-to-treat and a per-protocol analysis are performed.

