### **Dropout criteria:**

The following events/situations lead to the affected case being classified as a dropout and thus not being included in the per-protocol analysis:

- Serious violations of the project plan
- (With the exception of the test product:) Intake/consumption of (relevant amounts of) probiotics
- Incorrect inclusion
- Failure to follow up
- Unavailability of data required for the calculation of the primary endpoint parameters
- Unblinding
- Withdrawal of consent to participate in the study by the patient

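### The per-protocol set is primary for a difference-from-placebo hypothesis, so the main comparison rests on a set selected after randomisation and can be biased

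*Protocol*

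**What the plan says.** Section 6.1 (Data analysis and evaluation) commits to two analyses: "Both an intention-to-treat and a per-protocol analysis are performed".

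- The intention-to-treat set is "All inclusions (valid cases + dropouts").
- The per-protocol set is "All inclusions without meeting a drop-out criterion (all valid cases").
- The ranking is explicit, and no reason is given for it: "The per-protocol analysis is the primary evaluation concept".

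Under Dropout criteria, a case that meets any listed criterion is "classified as a dropout and thus not being included in the per-protocol analysis". There are seven criteria: serious violations of the plan, intake of relevant amounts of other probiotics, incorrect inclusion, "Failure to follow up", "Unavailability of data required for the calculation of the primary endpoint parameters", unblinding, and withdrawal of consent.

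The primary H1 in section 3.2 predicts higher vagal function and lower inflammation markers on probiotic than on placebo. The word superiority is not used, but a directional difference with no margin is a superiority hypothesis.

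**The concern.** In a randomised trial that sets out to show a difference, the primary comparison should keep participants in the arms to which they were allocated. That is what makes the arms comparable apart from chance. Six of the seven dropout criteria describe events that arise, or can arise, after allocation. Withdrawal and loss to follow-up may depend on tolerability or perceived benefit, hence on arm, and also on clinical course, hence on outcome. If that dependence differs between arms, the remaining participants are no longer comparable, and an apparent benefit can be created, enlarged or hidden.

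Three features of the protocol make exclusions foreseeable or open to judgement:

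- The intervention lasts three months, and after discharge patients take the product at home unsupervised (section 5.1).
- The criteria do not define what makes a violation serious or an amount of probiotic relevant.
- With 20 participants per group (section 6.2), a few exclusions can move a group mean.

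If the two analyses disagree, the protocol makes the per-protocol result the answer.

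**Working it through.** **1. The planned sample size.** Section 6.2 gives f = 0.2, alpha 0.05, 95% power, four groups and a repeated-measures within-between interaction, leading to 80 participants. The abstract gives four measurements. The text does not state the correlation between measurements or the sphericity correction, so 0.5 and 1 are assumed.

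- Noncentrality: λ = f²·N·m/(1−ρ) = 0.04 × 80 × 4 / 0.5 = 25.6
- Degrees of freedom: (4−1)(4−1) = 9 and (80−4)(4−1) = 228
- Power = 0.96, and 80 is the smallest multiple of four that reaches 95%

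The stated 80 therefore reproduces, and it contains no allowance for exclusions. On the same assumptions, a per-protocol set reduced by 10%, 20% or 30% (72, 64 or 56 participants) has power of 93.4%, 89.5% or 83.8%. The exclusion rates are assumed. So 80 at 95% power corresponds to analysing everyone randomised.

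**2. Which criteria act after randomisation.** Incorrect inclusion rests on baseline status. The other six arise or can arise later.

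**3. Possible bias, by direct arithmetic.** Assumptions, none from the protocol: no true effect, outcome SD of 1, probiotic against placebo pooled over patients and controls (n = 40 each), and exclusions in the probiotic arm only. The k excluded participants are on average s = 1 SD worse than their arm's mean.

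- Bias = k·s/(n−k)
- SE = √(1/(n−k) + 1/40)
- Two-sided rejection rate at 5% = P(Z > 1.96 − bias/SE) + P(Z < −1.96 − bias/SE)

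| Excluded | Bias | SE | Bias/SE | Rejection rate |
|---|---|---|---|---|
| 4 of 40 (10%) | 4/36 = 0.111 SD | √(1/36 + 1/40) = 0.230 | 0.484 | 0.077 |
| 8 of 40 (20%) | 8/32 = 0.250 SD | √(1/32 + 1/40) = 0.237 | 1.054 | 0.184 |

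**4. Equal exclusion rates in both arms.** A simulation with no true effect (40 against 40, two-sided t-test, 6,000 replicates per setting) excluded the same expected share from each arm. Exclusion was related to poor outcome in the probiotic arm and random in the placebo arm. The latent correlation of exclusion with outcome was varied. Cells show bias in SD and type I error.

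| Excluded per arm | Correlation 0.3 | Correlation 0.5 | Correlation 0.7 |
|---|---|---|---|
| 10% | 0.06; 5.9% | 0.10; 7.1% | 0.14; 8.6% |
| 20% | 0.11; 7.2% | 0.17; 10.3% | 0.24; 16.5% |
| 30% | 0.15; 8.1% | 0.25; 15.2% | 0.35; 27.5% |

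With the same outcome-related mechanism in both arms (20%, correlation 0.5), the bias was −0.004 SD and the type I error 4.7%. That is no bias and no inflation beyond simulation error.

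**The case against.** The case for leaving the plan alone has four parts.

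- **Intention-to-treat is also planned**, so a divergence would be visible. This stands as mitigation. It does not settle which result counts, because the protocol has already given precedence to per-protocol.
- **The trial is blinded**, with a matched placebo (section 5.1). Blinding makes arm-dependent exclusion less likely and protects decisions on who is a dropout. It does not prevent withdrawals that follow from tolerability or from worsening, and these can differ by arm under perfect blinding.
- **It is a pilot looking for a mechanism** (section 6.2 and abstract), where an on-treatment comparison has some rationale. That softens the point. But the protocol states a significance-based H0 and H1 and a 95% power calculation, so the primary result will be read as a test.
- **The illustration is simplified.** Step 3 puts every exclusion in one arm and fixes their outcome at 1 SD worse. It also reduces a four-group repeated-measures design to one two-group comparison. This stands: the figures show what could happen and do not forecast it.

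A reader might also infer more than the text supports:

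- *That the comparison is broken and the estimate biased.* Bias needs exclusion to relate to outcome differently by arm, and nothing in the protocol shows that it will.
- *That one missing measurement removes all of a participant's visits.* The criterion on unavailable data permits this reading, but does not say which visit or how many values it takes.
- *That patients who worsen drive exclusions throughout.* Half the planned sample are healthy controls.

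**Conclusion.** The point holds. The protocol itself fixes the per-protocol set as primary for a difference-from-placebo hypothesis, and builds that set largely on events that can follow randomisation. This is a stated choice, not a detail deferred to a statistical analysis plan. The supportable conclusion is that the primary estimate can be biased, not that it will be.

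The range runs from zero, when exclusion works the same way in both arms, to 0.11 SD (type I error about 8%) or 0.25 SD (about 18%) when only 10% or 20% of the probiotic arm, averaging 1 SD worse, is excluded. That is a worst case in that all exclusions fall in one arm. It is not a mathematical ceiling, since heavier or more strongly selective exclusion gives larger values, as step 4 shows. All of these figures rest on assumed exclusion rates and mechanisms. The direction could also be reversed if exclusion removed the better responders on probiotic.

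The change should be made before any data are seen, because it decides which result is the trial's answer.

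**What to change.** In section 6.1, make the intention-to-treat set primary, defined as all randomised participants analysed in the arm to which they were allocated, and make the per-protocol analysis supportive. The dropout criteria can stay as they are, because they would then define only the supportive set.

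State how incomplete outcomes are handled. The current intention-to-treat set includes dropouts, and some dropouts are defined by missing endpoint data, so the set cannot be analysed without such a rule. The method should keep participants with partial data. A baseline-adjusted mixed model using all observed visits is one option and is available in the planned SPSS software. It assumes that data are missing at random, so changing the set does not by itself remove bias from outcomes that are missing for reasons the observed data do not explain.

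The cost is protocol wording plus the missing-data statement. Both analyses are already planned, and no visit, procedure or sample size changes. The downside is that non-adherence may slightly dilute the estimate. The per-protocol result would still be reported beside it.

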### **Dropout criteria:**

The following events/situations lead to the affected case being classified as a dropout and thus not being included in the per-protocol analysis:

- Serious violations of the project plan
- (With the exception of the test product:) Intake/consumption of (relevant amounts of) probiotics
- Incorrect inclusion
- Failure to follow up
- Unavailability of data required for the calculation of the primary endpoint parameters
- Unblinding
- Withdrawal of consent to participate in the study by the patient

## 6.2 Considerations regarding the number of cases

This project is a pilot study. To the best of our knowledge, probiotic effects on vagus function in depressed patients have never been investigated before. A power analysis was performed using G\*Power 3.1.(29). In the F-tests category, the

"Repeated Measures ANOVA within-between interaction" was selected as the procedure. With a low effect size of 0.2, alpha 0.05 and 95% power, a total of 80 participants (20 participants per group) is required for 4 groups (healthy subjects: probiotic/placebo; depressed patients: probiotic/placebo).

[figure not shown]

Figure 3: Sample size calculation with G\*Power

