## **Abstract**

### **Justification:**

Depression is one of the most common and serious illnesses worldwide and has a significant negative impact on patients' quality of life and ability to work. Patients with depression exhibit changes in the gut microbiome and its metabolites, which in turn influence the gut-brain axis as a bidirectional communication system. A key component of this axis is the vagus nerve, which transmits information from the internal organs in the periphery to the central nervous system. Studies have shown that the function of the vagus nerve is impaired in patients with depression. At the same time, depressed patients often have a pro-inflammatory status, which is linked to the function of the vagus nerve in influencing the immune response. Animal models have shown that vagal afferents transmit information from intestinal bacteria directly to the central nervous system and can thus induce both anxious and depressive behaviour. Stimulation of the vagus nerve (which is currently used clinically as an invasive procedure for treatment-resistant depression) has been shown to improve depression and alleviate (neuro)inflammation. A pilot study from our working group has shown that the diversity of the gut microbiome in women correlates with the function of the vagus nerve ([name]/Oberascher et al., 2020, in prep).

**Relevance:** To date, no research has been conducted into whether and to what extent probiotics can influence the function of the vagus nerve. This new mechanism could be used to specifically alter the function of the vagus nerve with probiotics and provide a rationale for add-on therapy with probiotics ("psychobiotics").

**Design:** This monocentric study will investigate the effect of a multi-strain probiotic on vagus nerve function in 40 depressed patients and 40 healthy control subjects in a placebo-controlled setting. The study participants will receive either a probiotic or a placebo for 3 months, and the function of the vagus nerve will be determined at 4 time points using a portable ECG, which will be worn for 24 hours. In addition, inflammation markers (hs-CRP, IL-6) and the gut microbiome were determined using 16S sequencing. This is the first study worldwide to investigate the effects of a multistrain probiotic on the vagus nerve in depressed patients compared to healthy control subjects. The results of this study could contribute to a better understanding of the basis of probiotic effects on mental processes.

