### 3. Study procedure

#### Study design

This study is being conducted at the University Clinic for Psychiatry and Psychotherapeutic Medicine as a monocentric, randomised study. Randomisation is carried out by Allergosan (block randomisation). Patients at the University Clinic for Psychiatry who meet the inclusion criteria are invited to participate. Healthy control subjects will be recruited by Probando (probando.io) as well as via social media and notices on bulletin boards. A total of four **study visits** will take place. During the clinical visits, blood samples will be taken, psychological and cognitive tests will be conducted, and a clinical interview will be held to record any possible side effects and symptoms. The psychiatric diagnosis is made at the start of the study by a psychiatrist using the M.I.N.I. (Mini International Neuropsychiatric Interview [24]).

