#### **Follow-up appointment (i.e. after 3 months):**

- Blood sample
- Stool (can be brought along, max. 1 day old and stored in a cool place) including stool log
- Anthropometry
- Questionnaires
- Heart rate variability (device is attached and worn for 24 hours)

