##### H1:

A 4-week intake of a multi-species probiotic shows a significant increase in vagal function (measured by HRV, log RSA) and a significant decrease in inflammation parameters (IL-6, hsCRP) in subjects with depression and in healthy control subjects compared to placebo treatment.

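### The 80 participants at 95% power belong to a four-group by time interaction with complete data, not to the 4-week probiotic–placebo comparison that is the primary hypothesis

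*Protocol*

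**What the plan says.** Protocol section 6.2 uses the G*Power procedure "Repeated Measures ANOVA within-between interaction" and concludes: "With a low effect size of 0.2, alpha 0.05 and 95% power, a total of 80 participants (20 participants per group) is required". The calculation treats the two treatment arms within each population as separate groups, four in all. The correlation between measurements and the number of measurements are not in the text; they would be in the figure that is not shown.

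The primary hypothesis in section 3.2 reads: "A 4-week intake of a multi-species probiotic shows a significant increase in vagal function". It goes on to require a fall in IL-6 and hsCRP, compared with placebo, in depressed subjects and in healthy controls. Section 4.1 names logRSA, hs-CRP and IL-6 as the primary endpoints.

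On the number of measurements, the Abstract says that "the function of the vagus nerve will be determined at 4 time points using a portable ECG", and section 3 (Study design) says "A total of four study visits will take place". Written procedures follow for three visits only: Visit 1, Visit 2 at one month, and "Follow-up appointment (i.e. after 3 months").

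The Abstract plans 40 patients and 40 controls. Section 6.1 (Data analysis and evaluation) makes the per-protocol set primary and defines it as "All inclusions without meeting a drop-out criterion (all valid cases"). The dropout criteria include loss to follow-up, missing primary-endpoint data, unblinding, serious protocol violations and withdrawal of consent.

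**The concern.** The sample size is justified by one test and the hypothesis needs another. The within-between interaction with four groups asks whether any of the four mean profiles over time differ. Part of that is probiotic versus placebo; another part is depressed versus healthy. The patients are being treated as inpatients for depression, so a time course different from that of healthy volunteers is plausible without any probiotic effect. A significant result would then not support the primary hypothesis.

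The 80 described as required are also all the participants enrolled, so any exclusion from the primary set leaves fewer than section 6.2 requires. And an effect size labelled *low* may lead readers to think that the trial can detect small effects.

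**Working it through.** **Inputs.** From section 6.2: f = 0.2, alpha = 0.05, k = 4 groups, N = 80. From the Abstract: m = 4 measurements. Assumed: correlation rho = 0.5 and sphericity.

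**1. Reproducing the stated figure.** For the interaction, lambda = f² × N × m / (1 − rho), df1 = (k − 1)(m − 1), df2 = (N − k)(m − 1), with power from the noncentral F distribution.

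- N = 80, m = 4: lambda = 0.04 × 80 × 4 / 0.5 = 25.6; df 9 and 228; power 96.0%.
- N = 76, m = 4: power 94.8%. So 80 is the smallest balanced total that reaches 95%.
- m = 3 would need 92, and m = 2 would need 112.

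The match depends on rho. With m = 4, rho of 0.3, 0.4 or 0.6 gives 108, 92 or 64. N = 80 also reaches 95% with m = 3 if rho is about 0.56, and with m = 2 if rho is about 0.65.

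**2. What that test can pick up.** Suppose there is no probiotic effect, but patients change by g SD relative to controls from the second measurement on. The interaction effect is then f = g × √(1/4 × 3/16) = 0.2165 g.

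- g = 0.5: f = 0.108, lambda = 7.5, rejection probability 41%.
- g = 0.8: f = 0.173, lambda = 19.2, rejection probability 87%.

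A simulation of 4000 trials gives 41% and 88%, and 5.0% when there is no difference at all. Both values of g are assumptions. If the difference builds up linearly to 0.5 or 0.8 SD at the last measurement, the probabilities are 30% and 73%.

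**3. Loss of evaluable participants, stated 4 × 4 test.** The loss rates are assumed, as the protocol gives none.

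- 10% loss, N = 72: 93.4%.
- 20% loss, N = 64: 89.5%.

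**4. What f = 0.2 means at 4 weeks.** With baseline and one later value, a probiotic–placebo difference in change of delta gives interaction effects of ±delta/4. So f = delta/4, and f = 0.2 is delta = 0.8 SD. The SD of change is √(2(1 − rho)) = 1.0 at rho = 0.5. In the 4 × 4 layout, an effect constant from the second measurement on would have to be 0.2 / 0.2165 = 0.92 SD.

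**5. Power of the 4-week probiotic–placebo contrast at 0.8 SD, rho = 0.5.** Baseline adjustment reduces the residual SD to √(1 − 0.5²) = 0.866.

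| Evaluable | Change score | Baseline-adjusted |
|---|---|---|
| 40 vs 40, pooled | 94.2% | 98.3% |
| 36 vs 36, pooled (10% loss) | 91.7% | 97.1% |
| 32 vs 32, pooled (20% loss) | 88.3% | 95.3% |
| 20 vs 20, one population | 69% | 81% |

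**6. Detectable difference at 80% power, change scores, complete data.** About 0.63 SD with 40 vs 40 and 0.91 SD with 20 vs 20. Multiplying by 0.866 for baseline adjustment gives about 0.55 and 0.79 SD.

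**The case against.** A reader might infer that the trial simply lacks the power it claims. The documents do not support that. At the protocol's own f = 0.2, the pooled 4-week contrast has 94.2% power on change scores with complete data, within a point of the target. Baseline-adjusted, it still has 95.3% after 20% loss. The claim fails only on particular readings: if the effect must be shown in each population separately, or if change scores are used and participants are lost.

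A reader might also take three as the true number of measurements and quote the 91.8% power that the four-group test then has at N = 80. That is not established. The Abstract and section 3 both say four, and the visit figure is not shown. The written procedures leave a discrepancy to reconcile, not a proven count.

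The G*Power inputs are in a missing figure, so four measurements and rho = 0.5 are inferences. Section 6.1 names no confirmatory test, and a statistical analysis plan may do so; the 41% and 87% apply only if the interaction is that test. The loss rates are assumed, an intention-to-treat analysis is also planned, and the protocol calls itself a pilot.

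These points limit the size of the problem. What stands is that section 6.2 itself names a four-group interaction, allows for no loss, and gives no power for the comparison in the primary hypothesis. Pilot status does not excuse this, because 95% power is claimed all the same.

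**Conclusion.** The sample-size statement is wrong as a statement about the primary hypothesis. Its 80 and 95% are reproduced by a four-group by four-measurement interaction with complete data (rho = 0.5 and four measurements inferred). That test does not isolate probiotic from placebo and could be significant through diagnosis alone. With every enrolled participant counted as required and dropouts removed from the primary set, the stated test falls to 93.4% or 89.5% at an assumed 10% or 20% loss.

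For the randomised contrast at f = 0.2, the answer depends on choices that section 6.2 does not state. Pooled, power is close to or above 95%. Within either population it is 69% on change scores or 81% baseline-adjusted, so the 95% is not available if the primary hypothesis must hold in patients and in controls separately. All of this supposes a 0.8 SD difference in change, which is not a *low* effect.

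**What to change.** Rewrite section 6.2, with matching text in sections 3 and 3.2:

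- Name as primary test the single-degree-of-freedom probiotic–placebo contrast at 4 weeks, adjusted for baseline and diagnosis.
- State whether the populations are pooled or each must show the effect, and how logRSA, IL-6 and hsCRP are handled jointly (all required, any one sufficient with adjustment, or one ranked first).
- Restate power or the detectable difference for that contrast, giving the assumed correlation and the evaluable number (for example 64 to 72). The figures must match the model: those in step 6 are for complete data, and the baseline-adjusted ones are smaller than those for change scores.
- Drop the word *low* and give the effect in SD units of logRSA change.
- Reconcile the four time points and visits with the three visits that have a written procedure.

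The cost is some rewriting. No participants or data are added. The drawback for the sponsor is that the stated power may look less favourable, clearly so if each population must succeed.
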